### Data collection

Demographic information, including gender, age, education level, marital status and household income, will be collected at T0. All outcomes will be measured at T0, T1, T2 and T3 (Fig. 1). The primary and secondary outcome measures are described in details below:

#### Primary outcome

T1 will be chosen as the primary outcome endpoint as it represents the time at which we expect to observe the largest effect of intervention. Self-reported depressive symptoms will be measured by the validated the Chinese version Beck Depression Inventory-II (BDI-II) [20] which is more sensitive than PHQ-9 in measuring changes in depressive symptoms in clinical studies. The BDI-II is a 21-item inventory of depressive symptoms. The internal consistency and factor structure of the BDI-II has received extensive support among outpatient samples of adults which indicates that it is a very reliable and well validated scale to measure depressive symptom severity [20]. It is the premier instrument for the assessment of depressive symptom severity and the tracking of short-term changes in severity in outpatient settings.

#### Secondary outcomes

##### Anxiety symptoms

Anxiety symptoms will be measured by the Beck Anxiety Inventory [21], which is a self-report measure consisting of 21 items rated on a Likert scale from 0 to 3, representing ‘not at all’ to ‘severely’. It has satisfactory internal consistency in the Chinese population [21].

##### Quality of life

Quality of life will be measured by the Chinese version Medical Outcomes Study Short-Form Health Survey (SF-12) [22]. The SF-12 is a 12-item survey that measures health-related quality of life, including both physical and mental functioning and well-being. It is validated in local Chinese population [22].

##### Physical activity levels

Physical activity levels will be measured by the International Physical Activity Questionnaire – Short Form (IPAQ-SF) [23], which is a reliable and valid in the local Hong Kong population. The original IPAQ assesses the amount of exercise, physical activities and sitting time in the last 7 days. In addition, physical activity data obtained by the wrist trackers will be used to validate the responses to the IPAQ-SF. If there is any discrepancy, the research assistant will contact the participants for verification. We will further ask if their exercise habit in the last 7 days is different than their usual exercise amount.

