### Intervention: Online exercise programme

The design of the exercise class (duration and frequency) is modified from the class for diabetes and hypertension based on findings from recent systematic reviews on the effectiveness of physical activity intervention for improving depression and anxiety [8]. The 12-week EIM program aims to transform participants' exercise habits by fostering and maintaining behavioural changes through motivation, as well as providing relevant knowledge and experience. The online classes will be conducted by certified physical trainers who hold a post-secondary degree (or equivalent), possess a valid basic life support certificate, and have been certified by the Physical Fitness Association of Hong Kong after passing examinations. They have also completed specialized training to deliver the EIM program.

The 12-week EIM online class on the Zoom platform (details in Appendix 1) will enrol 11 to 18 patients per group and meet twice a week for 1 h each time. Each class contains a set of exercises including stretching, aerobic exercise and resistance training (combined exercise) and will be carried out according to specific protocol [17] (Appendix 1). Participants will receive reminders about each session via WhatsApp or telephone calls. After each class, home exercises were assigned to achieve a minimum of 150 min of exercise per week. Additionally, regular SMS or WhatsApp messages will be sent to remind and encourage participants to incorporate exercise into their daily routines. Furthermore, participants will also be provided with smartwatches to track their physical activities. The trainers can monitor participants' activity levels via trackers before each lesson, enabling them to motivate individuals and address barriers as needed, thereby offering regular reinforcement, social support, and problem-solving assistance. Zoom lessons will be recorded, and approximately 15% of these recordings will be reviewed by the investigator to ensure fidelity to the intervention.

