### Care as usual control

Participants in the both groups have unrestricted access to GOPCs for any health problem, including depressive symptoms. In Hong Kong, the general outpatient clinics provide primary care services at a low subsidized fee.

Participants assigned to the control group will receive medical care from GOPCs. In Hong Kong, individuals with subthreshold depression are managed in primary care setting instead of being referred to mental health specialists.

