##### Cost assessment

Costs using both provider and societal perspectives will be collected. The cost of healthcare service, the productivity loss of the participants and cost of caregiver will be self-reported by the participants. The cost of productivity loss of the participants will be estimated by the number of sick leave and the cost of each working days. The frequency of utilizing healthcare service and the cost of each visit including medication and transportation fee will be recorded. The cost of caregiver will be the money and time spent on taking care of the participants by caregivers. The cost of the online exercise intervention includes hiring cost of physical trainers, other administrative costs associated with the operation of the online exercise intervention programme, and costs of purchasing and maintaining the wearable trackers. The data from cost assessment will be used with the BDI-II and SF-12 scores for evaluating the cost-effectiveness of the online exercise programme.

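### IPAQ-SF answers are to be checked against wrist trackers that, as the article reads, only the exercise arm wears, so follow-up physical activity may be measured differently in the two arms

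*Protocol article*

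**What the plan says.** Under Physical activity levels, the protocol article makes the IPAQ-SF the measure of this secondary outcome. It then says that "physical activity data obtained by the wrist trackers will be used to validate the responses to the IPAQ-SF", and: "If there is any discrepancy, the research assistant will contact the participants for verification". Neither sentence names an arm.

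Devices are handed out in one place only, the section Intervention: Online exercise programme: "participants will also be provided with smartwatches to track their physical activities". That section also gives them a role in the treatment. Trainers can look at "activity levels via trackers before each lesson, enabling them to motivate individuals and address barriers as needed".

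The Cost assessment section opens its list of programme costs with "The cost of the online exercise intervention includes hiring cost of physical trainers" and closes it with "costs of purchasing and maintaining the wearable trackers".

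On the other arm, Care as usual control says: "Participants assigned to the control group will receive medical care from GOPCs". It mentions no device.

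The Data collection section schedules every outcome at T0, T1, T2 and T3. The baseline IPAQ-SF category is one of the stratification factors for randomisation.

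**The concern.** A comparison between randomised arms needs the outcome to be obtained in the same way in both. A check against a device can flag a discrepancy only in someone who wears the device. If only the exercise arm does, its follow-up self-reports pass through a query that control self-reports never meet. Any change in the answers that the query brings about becomes part of the apparent treatment effect on physical activity.

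Randomisation does not protect against this, because the difference arises after allocation. Adjusting for baseline does not help either, because T0 answers are unverified in both arms. The mixed models planned for the secondary outcomes look at change over time, so a shift confined to one arm after T0 would appear as a difference in change.

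What is at stake is a secondary outcome, but a useful one: physical activity is what the programme sets out to alter, and readers will turn to it to interpret the BDI-II result.

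**Working it through.** **Plan's own figures.** The article gives no mean, standard deviation, target difference or reporting error for the IPAQ-SF, so there is nothing to reproduce for this outcome. Its one calculation, the sample size, concerns BDI-II. It reproduces: 3.5 points with SD 8.95 (effect size 3.5/8.95 = 0.39), two-sided 0.05 and 80% power need 103.6, hence 104 per group by the t-test; 104/(1 − 0.20) = 130 per group, 260 in total. Nothing here touches it.

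**Who can be queried, and when.**

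| Question | What the article gives | What follows |
|---|---|---|
| Who gets a tracker? | Issue described only in the intervention section; cost listed only under the programme; usual-care section silent | Exercise arm only, by inference |
| When? | As part of the programme, which follows allocation; the T0 IPAQ-SF is needed for stratification | No programme tracker exists at T0 |
| What triggers a contact? | A discrepancy between tracker and IPAQ-SF | Possible only for tracker wearers |
| What happens to the answer? | Verification; nothing further | Revision is possible but not stated |

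The Feasibility and acceptability section fits the same reading: it uses tracker data to supplement class attendance and retention. The opposite reading, trackers in both arms, would create problems of its own. Controls would receive a device that the trainers use as part of the programme, and the cost section would charge a shared item to one arm.

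Taken together:

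- T0: raw self-report in both arms.
- Follow-up, control arm: raw self-report.
- Follow-up, exercise arm: self-report that may be queried against a device and possibly revised, for as long as the device is worn.

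**Illustration of how the bias would act (all inputs assumed).** Let true activity be equal in both arms, let self-report exceed it by a fraction *b* in both, and let the query remove a share *c* of that excess in the exercise arm only. The apparent relative difference, exercise against control, is

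(1 + *b*(1 − *c*)) / (1 + *b*) − 1.

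| *b* | *c* = 0.25 | *c* = 0.50 | *c* = 1.00 |
|---|---|---|---|
| 0.10 | −2.3% | −4.5% | −9.1% |
| 0.30 | −5.8% | −11.5% | −23.1% |
| 0.50 | −8.3% | −16.7% | −33.3% |

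If participants under-report instead, or if queries raise answers, the sign reverses: with *b* = −0.10 and *c* = 1, the result is 1/0.90 − 1 = +11.1%. If no answer is ever altered, *c* = 0 and the bias from this source is zero. The table shows the mechanism. It does not estimate the bias in this trial.

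**The case against.** The strongest reply is that much of this is inference. No sentence says that controls have no tracker. The usual-care section describes clinical care rather than measurement, so its silence is weak evidence in a condensed article. Costing trackers to the programme does not exclude devices issued to controls for measurement. The article also does not say that a verified answer replaces the reported one, and rules of that kind usually sit in a fuller document that is not shown.

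This rightly limits what can be claimed. A reader might infer more in four respects, and the documents do not support it:

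- **That exercise-arm answers will be corrected.** Only contact for verification is stated. Revision is a possibility.
- **That assessor blinding is compromised.** The verification contact falls to the research assistant. Under Randomization, concealment and blindness, a research assistant tells participants their allocation, so that role can already be unblinded. Nothing says the caller assesses outcomes.
- **That T1, T2 and T3 are all affected.** The article does not say whether trackers are worn once the 12-week programme ends.
- **That the bias has a known size or direction.** It has neither. If over-reporting were the rule, the effect would be to understate the programme's benefit on activity.

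What survives is not a complaint about missing detail. The article states a procedure which, read with its own account of who gets the devices, can operate in one arm only. It is also fair to say that physical activity appears in none of the stated objectives or hypotheses and that the article calls its secondary analyses exploratory. That limits the weight of the point without removing it.

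**Conclusion.** The concern holds in a limited form. As the article reads, follow-up IPAQ-SF answers can be queried, and possibly revised, in the exercise arm, while control answers and all T0 answers remain raw self-report. The between-arm comparison of physical activity may therefore be biased, by an amount and in a direction that the documents do not allow to be computed.

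This rests on two assumptions: that trackers go only to the exercise arm, which is strongly indicated but not stated, and that a query can change the value analysed, which is left open. If either fails, this bias disappears. The primary BDI-II analysis and the sample size are unaffected. Because the point concerns one secondary outcome and the remedy is cheap, it is worth settling before the data are analysed.

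**What to change.** In Physical activity levels, state that:

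1. all between-arm IPAQ-SF analyses use the answers as first reported, in both arms;
2. any value obtained after a tracker query is kept in a separate field and does not replace the reported one;
3. tracker data, and their agreement with the IPAQ-SF, are reported descriptively within the exercise arm only.

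One sentence saying which participants wear trackers, and over what period, would remove the need for inference. If controls do in fact receive them, the intervention and cost sections need to be reconciled with that.

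As a precaution only, verification contacts should not be made by the blinded outcome assessors. The documents do not show that they would be.

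The cost is a few lines of wording and one extra data field, with no added devices, visits or participants. The downside is real: discrepancies known to exist in the exercise arm stay in the comparative outcome. For a between-arm contrast, error handled alike in both arms is preferable to a check that can reach only one.

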##### Feasibility and acceptability

Recruitment rate will be determined by the ratio between the total number of participants randomised and the total number of persons meeting inclusion criteria. Feasibility will be examined by tracing class attendance and retention, supplemented with data of the participants’ physical activity levels recorded from the wearable trackers. Acceptance will be assessed by collecting evaluation form immediately after the intervention (Appendix 2).

##### Medication use and health service utilization

All medications associated with an intention to improve mood or mood-related symptoms will be recorded at follow-up. These include anticonvulsants, antidepressants and anxiolytics including benzodiazepines. Utilization of health services including visits to primary care doctors (both private and public) or accident and emergency units, visits to any specialist outpatient clinics, use of other psychiatric services such as psychologists, social workers or occupational therapists, and hospitalizations will be recorded at all visits to see whether there are changes between groups on health services utilization. The electronic patient records of the Hospital Authority for the utilization of public healthcare services will be checked, supplemented by the participants’ self-report.

##### Cost assessment

Costs using both provider and societal perspectives will be collected. The cost of healthcare service, the productivity loss of the participants and cost of caregiver will be self-reported by the participants. The cost of productivity loss of the participants will be estimated by the number of sick leave and the cost of each working days. The frequency of utilizing healthcare service and the cost of each visit including medication and transportation fee will be recorded. The cost of caregiver will be the money and time spent on taking care of the participants by caregivers. The cost of the online exercise intervention includes hiring cost of physical trainers, other administrative costs associated with the operation of the online exercise intervention programme, and costs of purchasing and maintaining the wearable trackers. The data from cost assessment will be used with the BDI-II and SF-12 scores for evaluating the cost-effectiveness of the online exercise programme.

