### Statistical analysis

Baseline characteristics of the two groups will be compared using chi-square test for categorical variables and independent samples t-test for continuous variables. Analysis of covariance (ANCOVA) for the BDI-II score at T1 will be conducted as the primary analysis, with the BDI-II score at T0 and other characteristics with significant between-group difference at T0 as covariates in the model for sensitivity analyses. Effect size estimates will be obtained for the primary outcome, with the between group effect sizes (Cohen’s d) being calculated using the mean differences from baseline and the SDs of the two groups at each time point. For the secondary analysis, linear mixed models (LMM) with random intercept will be applied to investigate the significant changes over time, for both primary and secondary outcome measures. The LMM approach is in line with the intention-to-treat principle, to include all subjects for the analysis and use all available data to assess the treatment effect over time. Maximum likelihood estimation (MLE) will be employed to handle missing data in the analyses with LMMs. A sensitivity analysis will be conducted using imputed data generated by multiple imputation. Furthermore, compliance with prescribed exercises will be added into the models to explore if this is predictor of changes in health outcomes.

In the cost-utility analysis, utility will be measured with quality adjusted life years (QALYs) based on SF-12 using the Hong Kong weights. The area under curve approach will be used to calculate the utilities at follow-ups after adjusting for baseline utility. In the cost-effectiveness analysis, remission of depressive symptoms (BDI-II score of < 14) will be used as outcome. Using both provider and societal perspectives, incremental cost-effectiveness ratio (ICER) will be calculated by dividing cost difference of two groups by between-group effect difference. We will use bootstrapping technique to assess the uncertainty of the ICER estimate. Due to the lack of a local willingness-to-pay threshold, we will generate cost-effectiveness acceptability curves to evaluate the probability of cost-effectiveness of the proposed intervention.

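### Healthcare cost is taken from participants' self-report while public outpatient care carries a low subsidised fee, so the provider's cost of routine public care would be missing from the provider ICER and the subsidised share from the societal ICER

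*Protocol article*

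**What the plan says.** Four places in the protocol article bear on this.

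- **Cost assessment, perspective:** "Costs using both provider and societal perspectives will be collected".
- **Cost assessment, source:** "The cost of healthcare service, the productivity loss of the participants and cost of caregiver will be self-reported by the participants". On visits it adds: "The frequency of utilizing healthcare service and the cost of each visit including medication and transportation fee will be recorded". The programme's own cost is listed separately, as trainers, administration and wearable trackers, and is not among the self-reported items.
- **Care as usual control:** "Participants in the both groups have unrestricted access to GOPCs for any health problem, including depressive symptoms", and "In Hong Kong, the general outpatient clinics provide primary care services at a low subsidized fee". No amount and no subsidy share is given.
- **Medication use and health service utilization:** "The electronic patient records of the Hospital Authority for the utilization of public healthcare services will be checked", with self-report as a supplement. This supplies volumes of use. Nothing is said about prices.

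Statistical analysis then uses the costs: "Using both provider and societal perspectives, incremental cost-effectiveness ratio (ICER) will be calculated", as the cost difference between groups over the effect difference, with bootstrapping and acceptability curves for uncertainty.

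**The concern.** The named source does not fit the announced perspective. What a participant knows about a subsidised visit is the charge. For the provider, that charge is a payment received, not the resource cost of the visit. For society, the resource cost includes the part that the subsidy covers. A self-reported charge therefore gives neither.

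The two arms' costs would also be built on different footings. The exercise programme is costed from its delivery inputs. Any change in public care that it brings about would be counted at what the patient pays. A saving or an increase in routine public care would then enter the ICER numerator at a fraction of its real value.

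Cost-effectiveness is a stated secondary objective and a stated hypothesis, so this affects a planned conclusion. Bootstrapping describes sampling uncertainty around whatever costs are entered and does not repair a systematic error in valuation. The acceptability curves inherit the same error.

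**Working it through.** The article states no cost, fee, unit cost or ICER, so there is no figure of its own to reproduce. The check is a reading of the sections side by side, followed by an illustration with assumed inputs.

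**1. What each cost component would contain under the stated sources**

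| Component | Stated source | Provider cost captured? | Societal cost captured? |
|---|---|---|---|
| Programme delivery | Trainer, administrative and tracker costs | Yes | Yes |
| Public outpatient visits, number | Hospital Authority records plus self-report | Volume only | Volume only |
| Public outpatient visits, cost | Participant self-report; fee is low and subsidised | No | Patient's share only |
| Sick leave | Reported days times cost of a working day | Not a provider cost | Yes |
| Caregiver time and money | Participant self-report | Not a provider cost | Yes |

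The gap is in the third line.

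**2. Share of the public-care difference that is captured**

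Let *f* be the fee divided by the full provider cost of the same service. Valued at the fee, a between-arm difference in public care is captured in the proportion *f* and missed in the proportion 1 − *f*. The article gives no *f*. With assumed values:

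- *f* = 0.10: 1 − 0.10 = 90% missed
- *f* = 0.25: 1 − 0.25 = 75% missed
- *f* = 0.50: 1 − 0.50 = 50% missed

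These percentages describe the public-care component, not the ICER.

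**3. Effect on the cost difference**

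A second assumption is needed. Let *s* be the between-arm difference in full public-care cost, as a share of intervention cost per participant, with intervention cost set to 1.

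- Use falls: full-cost numerator 1 − *s*; fee-based numerator 1 − *sf*; ratio (1 − *sf*)/(1 − *s*).
- Use rises: full-cost numerator 1 + *s*; fee-based numerator 1 + *sf*; ratio (1 + *sf*)/(1 + *s*).

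Fee-based numerator divided by full-cost numerator:

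| *s* | *f* | Use falls | Use rises |
|---|---|---|---|
| 0.10 | 0.05 | 0.995/0.90 = 1.11 | 1.005/1.10 = 0.91 |
| 0.10 | 0.50 | 0.95/0.90 = 1.06 | 1.05/1.10 = 0.95 |
| 0.25 | 0.10 | 0.975/0.75 = 1.30 | 1.025/1.25 = 0.82 |
| 0.50 | 0.05 | 0.975/0.50 = 1.95 | 1.025/1.50 = 0.68 |
| 0.50 | 0.50 | 0.75/0.50 = 1.50 | 1.25/1.50 = 0.83 |

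Over *f* from 0.05 to 0.50 and *s* from 0.10 to 0.50, the ratio runs from 1.06 to 1.95 if use falls and from 0.68 to 0.95 if use rises. With a given positive effect difference the ICER scales by the same factor. The programme would look less cost-effective than it is in the first case, and more so in the second. In the societal analysis, productivity and caregiver terms also enter the numerator, so these factors do not carry over directly.

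**The case against.** The best defence is that self-reported need not mean valued at the fee. Productivity loss stands in the same sentence, yet it is then valued as reported sick leave times the cost of a working day. Healthcare could likewise be a reported or recorded quantity times a unit cost chosen by the analyst, and the article never says outright that a public visit will be priced at the patient's charge. It is also a condensed article, and a unit-cost source is the sort of detail that a full protocol or health-economic plan would hold.

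Part of this stands. The absence of a unit-cost table is no fault in an article, and a fuller plan may apply provider costs. But the article does not leave the source open. For productivity it spells out a quantity and a price. For healthcare it lists the cost itself as self-reported, and the items it names within visit cost, medication and travel, suggest what a patient pays. The sentence needs correcting even if the fuller plan is right.

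Other limits also stand. The low fee is stated only for general outpatient clinics, so extending it to emergency, specialist or inpatient care is an assumption. Private care is unaffected by the subsidy argument. The objective is secondary, and the record counts are already planned, so proper valuation remains possible at analysis.

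Three stronger readings are tempting, and the article does not support them:

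- **That the provider ICER contains no provider cost.** Programme delivery cost is in it; only the provider's cost of routine public care is missing.
- **That the two sections contradict each other on visit frequency.** The cost section says only that frequency will be recorded and names no source for it. The utilisation section supplies one for public care.
- **That recall error over the long follow-up interval distorts public visit counts.** The electronic records are to be checked for these. Recall remains an issue for private care, where self-report is hard to avoid.

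**Conclusion.** The point holds in a limited form. As written, the stated source for healthcare cost cannot deliver the provider's cost of routine public outpatient care, and it leaves the subsidised share out of societal cost. Between-arm differences in that care would be undervalued in both ICERs.

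The direction is unknown, because it depends on whether the programme lowers or raises public service use. The size cannot be derived from the article. The factor of 0.68 to 1.95 on the provider cost difference, and the missed shares of 50% to 90%, rest wholly on assumed fee shares and assumed differences in use. A reader might take the missed share as the bias in the ICER. It is not, because it applies to one component only; if public use does not differ between arms, the cost difference is unaffected.

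The primary outcome and its analysis are untouched. The point should be corrected because it bears on a stated secondary objective and hypothesis.

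**What to change.** In Cost assessment:

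- Value public service use as counts from the Hospital Authority records times full, unsubsidised provider unit costs, in both perspectives.
- Do not add the patient's fee on top of a full unit cost, which would count it twice.
- Limit self-report to private care, travel, sick leave and caregiver time and money.
- State that the electronic records described under Medication use and health service utilization are the source of public visit frequency.

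The cost is a few sentences, a unit-cost table with its source and price year, and slightly more analysis work. The records are already to be checked, so no new data collection from participants is needed. If a fuller economic plan already does this, only the article's sentence on self-reported healthcare cost needs to be brought into line.
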